### 2. Research topic

The impact of mulberry leaf extract at three different levels on reducing the glycemic index of white bread.

### 3. Research background

Carbohydrates are very commonly found in many kinds of food. According to whether they can be utilized by the body, they are divided into two types: available and unavailable carbohydrates. Their different composition patterns are directly related to the glycemic index (GI). GI is an effective index to measure the post-prandial blood glucose response caused by food, and is a food physiological parameter based on human data. After 40 years of research, it is found that low (GI<55) food has a very significant effect on nutrition intervention for chronic diseases (diabetes, hyperlipidemia, obesity, etc.), and also has a positive effect on sports nutrition, skin health, children's cognitive development, etc. Therefore, it is of great clinical significance to explore the combination pattern of different types of dietary fiber, sugar alcohol and other carbohydrate components with available carbohydrates, and the relationship between the combination pattern and the possible blood glucose response after food ingestion. The promotion of low GI diet is conducive to the development of food nutrition attribute research, and therefore to promote consumers to make consumption choice.

At present, the ISO26642:2010 is the international method for food GI determination. In view of the epidemic status of chronic diseases, the important role of dietary intervention in the prevention, control and treatment of diabetes, and the research needs of many product enterprises, the purpose of this study is to systematically evaluate the GI value of different composition modes of carbohydrate products/foods and their impact on short-term blood glucose metabolism of human body by following the international standard test method ISO26642:2010 and standard process.

In recent years, the research and development of low GI products have increased day by day. Among them, the role of functional plant extracts on glucose metabolism pathway and the research and development of low GI foods are considered to have great potential and research significance. The mulberry leaf extract has the effective component 1-deoxynojirimycin (DNJ). It belongs to a natural alkaloid azo sugar, which can be regarded as a competitive  $\alpha$ -Glucosidase inhibitor — Competitive inhibition of carbohydrate substrate and  $\alpha$ -binding of glucosidase, therefore to slow down the decomposition and absorption of carbohydrates in the small intestine, thus inhibiting the drastic fluctuation of postprandial blood sugar.

At present, there are not many studies on the efficacy of mulberry leaf extract at home and abroad, and the GI related research of adding different concentrations of mulberry leaf extract to real food is still relatively blank. Therefore, this experiment is an exploratory study of the effect of mulberry leaf extract using bread as food medium on blood glucose production index.

### 4. Research purpose:

This study aims to explore the addition of mulberry leaf extract on the glycemic index and sensory quality of white bread, and analyse the dose-effect relationship.

#### 5. Selection of study population

Subjects for the study will be aged between 18 and 40 inclusive with no known medical condition and otherwise must fulfil the inclusion and exclusion criteria.

##### ① Inclusion criteria

Participants must be healthy males or non-pregnant females, non-lactating and aged 18 to 60 years old.

Participants with a BMI between 18.5 and 24.0 kg/m^2.

Able to tolerate fasting for at least 10 hours

##### ② Exclusion criteria

Participants with impaired glucose tolerance or known history of diabetes mellitus or the use of antihyperglycemic drugs or insulin to treat diabetes and related conditions.

Suffer from any chronic diseases, such as AIDS, hepatitis, renal or heart disease or any other serious complications that may interfere with glucose metabolism.

Participants using any medication (eg steroids, protease inhibitors or antipsychotics, oral contraceptives, acetylsalicylic acid, etc.) or certain nutrition supplements that would interfere with the nutrient digestion, absorption, or glucose tolerance.

Participants having gastrointestinal diseases that may interfere with nutrient absorption, distribution, metabolism, excretion, intolerance to the study products and have known food allergies.

A major medical or surgical event requiring hospitalisation within the preceding 3 months.

#### 6. Sample size estimation

The protocol of ISO 26642:2010 indicated 10 healthy subjects would be selected for a food GI determination, with the assumption of a dropout rate of 20%, at least 12 subjects were required to ensure a data-set of 10 subjects at each GI test.

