#### 8. Research scheme

This study is exploratory. The specific research design is shown in the figure below.

[figure not shown]

Twelve subjects were randomly selected from 30 subjects to participate the GI tests of the experiment groups, and 18 subjects participated in the test of control group. The investigator followed the specified randomization procedures of the protocol and ensured that the randomization code is broken only in accordance with the requirements of the protocol.

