⑭Used needles are thrown into the biohazard collection container. Any other contaminated waste is also disposed of in the appropriate container.

⑮Ensure test record is complete and accurate.

⑯Direct participants to snack area if they want a snack before leaving.

⑰Disinfect tables and kitchen counters with 70% ethanol solution.

⑱Participants will be reimbursed for their time participating in the study. If a participant withdraws from the study or becomes ineligible and are withdrawn by the investigator prior to completing the full study, they will be compensated for portions of the study completed to that point. If this occurs, the participant will be replaced in order to maintain a minimum of twelve (12) participants with complete data for statistical validity. The randomization sequence for the replacement will be the same as the participant who drops out from the study.

Note: A wash out period of three (3) days (72 hours) is required between two different tests.

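### Section 6's dropout allowance is miscalculated (20% dropout calls for 13 starters, not 12, to leave 10), and Section 10 sets a different completer target and a different way of handling dropout

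*Protocol*

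**What the plan says.** Three places in the protocol bear on this.

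- **Section 6 (Sample size estimation)** takes its base number from the GI testing standard, which it says "indicated 10 healthy subjects would be selected for a food GI determination". It then builds on the "assumption of a dropout rate of 20%, at least 12 subjects were required to ensure a data-set of 10 subjects at each GI test". Here 12 is the number who start, 10 is the number needed at the end, and dropout is absorbed by enrolling more than are needed.
- **Section 8 (Research scheme)** fixes the number used: "Twelve subjects were randomly selected from 30 subjects to participate the GI tests of the experiment groups".
- **Section 10 (Standard operation process), step 18** provides that anyone who withdraws or is withdrawn before finishing will be replaced, "in order to maintain a minimum of twelve (12) participants with complete data for statistical validity". It adds: "The randomization sequence for the replacement will be the same as the participant who drops out from the study". Here 12 is the number who finish, and dropout is handled by replacement.

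**The concern.** There are two linked problems.

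The first is arithmetic. A 20% dropout rate applies to those who start, so the number needed at the end must be divided by the retained fraction. Section 6 appears to have added 20% to the number of completers instead, which gives too small an allowance. The figure is offered as a guarantee of 10 data-sets, and 10 is the number the protocol takes from the standard it follows.

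The second is consistency. Section 6 treats 10 complete sets as the requirement. Section 10 says validity needs 12. If 12 are needed, the target in Section 6 is too low; if 10 suffice, the reason given in Section 10 is not correct. The protocol gives no statistical basis for 12 completers. With replacement in force, the 20% allowance also has no work to do, so the rationale in Section 6 is not what secures the final number.

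What is at stake is the stated justification for the sample size and the clarity of the completion rule, not the size of any treatment effect or error rate.

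**Working it through.** **Inputs**

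- Completers required per GI test: 10 (Section 6).
- Assumed dropout: 20% (Section 6).
- Stated number to start: at least 12 (Section 6); twelve in use (Section 8).
- Completer minimum in the operating procedure: 12, reached by replacement (Section 10, step 18).
- No power, effect size or standard deviation enters the calculation. The number is the standard's 10 plus a margin.

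**Step 1: reproduce the plan's figure.** Completers x (1 + dropout) = 10 x 1.20 = 12. This matches exactly.

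**Step 2: check it forwards.** Starters x (1 - dropout) = 12 x 0.80 = 9.6, which is 0.4 below 10. Put the other way, 20% of 12 is 2.4 dropouts, but only 2 can be lost if 10 are to remain.

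**Step 3: usual inflation.** Completers / (1 - dropout) = 10 / 0.80 = 12.5, rounded up to 13. Expected completers are then 13 x 0.80 = 10.4. The gap from the plan is one subject.

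**Step 4: dropout rate that 12 does support.** 1 - 10/12 = 16.7%.

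**Step 5: how far 12 starters secure 10 if nobody is replaced.** Assume each subject drops out independently with probability 0.20. Independence is an assumption of this check; the protocol does not state it. The number of completers from 12 starters is then Binomial(12, 0.80):

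- P(10) = 66 x 0.8^10 x 0.2^2 = 0.283
- P(11) = 12 x 0.8^11 x 0.2 = 0.206
- P(12) = 0.8^12 = 0.069
- P(at least 10) = 0.558

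The same calculation for other numbers of starters:

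| Starters | Expected completers | P(at least 10 completers), no replacement |
|---|---|---|
| 12 | 9.6 | 0.56 |
| 13 | 10.4 | 0.75 |
| 14 | 11.2 | 0.87 |
| 15 | 12.0 | 0.94 |

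**Step 6: apply the Section 10 rule.** If every dropout is replaced until 12 have complete data, the number of completers is 12 whatever the dropout rate. That meets both the 12 of Section 10 and the 10 of Section 6. The 20% inflation then makes no difference to the data delivered. For comparison, 12 completers without replacement would need 12 / 0.80 = 15 starters.

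**Step 7: the two sections side by side**

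| | Section 6 | Section 10, step 18 |
|---|---|---|
| Meaning of 12 | subjects starting | subjects with complete data |
| Completers required | 10 | 12 |
| Dropout handled by | over-enrolment | replacement |

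**The case against.** The strongest defence is the replacement rule. Followed as written, it turns 12 starters into 12 complete sets, so the 10 are delivered and the two sections can be satisfied together. This stands, and it sets the limit of the point. A reader might infer from 12 x 0.80 = 9.6 that the sample size is inadequate, or that the trial has only about a 0.56 chance of reaching 10 completers. The documents do not support either inference, because both figures describe a trial without replacement and this protocol provides for it.

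It can also be said that the slip is one subject, that Section 6 says at least 12 and so does not exclude 13, and that 2.4 dropouts might be rounded to 2. The size is conceded. The wording does not rescue the figure, since Section 8 settles on twelve. Rounding 2.4 down to 2 amounts to an allowance of 16.7%, not the 20% stated.

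A further defence is that Section 6 is only a planning rationale, with no instruction to stop at 10, while Section 10 is the operating rule and is explicit. That is largely fair: staff who follow Section 10 know to continue to 12, so it would overstate matters to say they have no usable instruction. What remains is that the protocol gives two different numbers as the requirement and appeals to statistical validity for the larger one without support.

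Finally, Section 8 calls the study exploratory and the number is not a power calculation, so no loss of power or precision has been shown. That also stands.

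**Conclusion.** The point holds as a minor error, wrong as written. On Section 6's own inputs, 12 subjects do not ensure 10 at 20% dropout: they leave 9.6 on average, the correct inflation is 13, and 12 subjects tolerate 16.7%. Separately, Sections 6 and 10 disagree on the completer target (10 against 12) and on how dropout is handled (over-enrolment against replacement), and the second mechanism makes the first redundant.

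The arithmetic rests only on figures in the protocol. The 0.56 rests in addition on independent dropout and on no replacement, so it measures how little Section 6 secures by itself and does not forecast this trial. Whether 12 is enough is not called into question, provided the replacement rule is carried out.

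**What to change.** 1. **Make the Section 6 figure true.** Either say that 12 subjects allow 2 dropouts (16.7%) and still leave 10, or keep 20% and say 13. In either case drop the claim that the number ensures 10: without replacement, and with independent 20% dropout, even 13 gives at least 10 completers with probability only 0.75.
2. **Reconcile Sections 6 and 10.** State one minimum number of participants with complete data and one way of handling dropout, in the same terms in both places. If replacement stays, say that 12 is the completer target reached by replacement and remove the dropout inflation from Section 6. If over-enrolment is the mechanism, state 10 as the minimum in Section 10 as well. Either way, give the basis for the chosen minimum or remove the appeal to statistical validity.

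The cost is about two sentences of protocol text. No extra participants are needed if 12 is kept; choosing the 13-at-20% wording as the enrolment number would add one.

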#### 7. Measurement index

The glucose values will be plotted against time and the Incremental Area Under Curve (iAUC) will be determined. GI will be calculated by expressing each participant's glucose iAUC for the test product as a percentage of the same participant's average iAUC for the reference food, as illustrated in the formula below.

$$GI = \left( \frac{\text{iAUC of test product}}{\text{Average iAUC of reference food}} \right) * 100$$

#### 8. Research scheme

This study is exploratory. The specific research design is shown in the figure below.

[figure not shown]

Twelve subjects were randomly selected from 30 subjects to participate the GI tests of the experiment groups, and 18 subjects participated in the test of control group. The investigator followed the specified randomization procedures of the protocol and ensured that the randomization code is broken only in accordance with the requirements of the protocol.

#### 9. Ethics

The ethical approval for the study was obtained at the Chinese Academy of Medical Sciences and Beijing Union Medical College Hospital Ethics Review Committee (protocol code: HS-1763, first issued: November 27, 2018, latest updated on September 27, 2021).

#### 10. Standard operation process

The test was carried out in strict accordance with ISO 26642:2010 standard. In this experiment, blood was taken from the fingertip of a disposable blood sampling needle.

[Each GI test cycle]

- ①Set up participant's testing area with labels, test record sheet, alcohol swabs, lancets, finger prick device and timer.
- ②Record weight of each participant with shoes off upon arrival for the test each time.
- ③Fill out top section of blood glucose test record and double check for accuracy.
- ④Label tube with -5, 0 labels containing participant's initials, date and test food. The participants' identity will be subsequently decoded for sample analysis.
- ⑤Ensure participant is using own personalised blood-taking supplies and is familiar with safety procedures as outlined in consent form.
- ⑥Wipe participants finger with alcohol pad, then prick finger for fasting samples. Note: The capillary blood samples will be collected by trained research staff or phlebotomist.
- ⑦Collect 350  $\mu$ L of blood in test tube and mix blood with small amount of anti-coagulant at the bottom of the tube by rolling between hands. If glucose strips are used, blood is directly dropped on the strip and the values read immediately.
- ⑧Then the second fasting sample is taken at 0 minute and blood is collected accordingly. Taking 2 samples within 5 minutes is acceptable.
- ⑨Serve reference food/test food to the participant according to the study protocol with 250 mL of water
- ⑩Start timer with the first bite of test meal. Timers should be set at count down or count up to 2 hours.

⑪Make sure participant consumes test food or reference food and water within 5 to 10 minutes. However, if the food cannot be consumed in 10 minutes, the participant should try to consume the entire food, if possible, even if it takes longer than 10 minutes. Take as long as required to consume the entire test food or reference food. Participant may have to stop eating to take the 10 minute finger prick and continue eating.

⑫Record time taken to eat entire meal on the test record sheet.

⑬Prick finger, collect blood, roll tube, label tube, place in fridge. Continue this step for 30, 45, 60, 90, and 120 minutes, ensuring all tubes are properly labeled. If glucose strips are used, no need to collect blood, but can be analysed immediately.

⑭Used needles are thrown into the biohazard collection container. Any other contaminated waste is also disposed of in the appropriate container.

⑮Ensure test record is complete and accurate.

⑯Direct participants to snack area if they want a snack before leaving.

⑰Disinfect tables and kitchen counters with 70% ethanol solution.

⑱Participants will be reimbursed for their time participating in the study. If a participant withdraws from the study or becomes ineligible and are withdrawn by the investigator prior to completing the full study, they will be compensated for portions of the study completed to that point. If this occurs, the participant will be replaced in order to maintain a minimum of twelve (12) participants with complete data for statistical validity. The randomization sequence for the replacement will be the same as the participant who drops out from the study.

Note: A wash out period of three (3) days (72 hours) is required between two different tests.

#### 11. Statistical analysis methods

All statistical analyses were performed using SAS version 9.4. The blood glucose data were calculated from the point values of all the time spots of every participant, and the means and standard deviation (SD) were calculated for the normality test. All data were processed and compared using origin 2021 and Graph Prism 7.0. Data were analyzed by one-way ANOVA and paired t-test and differences with values of  $p < 0.01$  or  $p < 0.05$  were considered significantly differences.

##### ①Blood glucose measurement

Blood glucose level analysis instrument: Beckman Coulter AU480 automatic spectrophotometric analyzer with internal controls (CV<3.6%).

Blood collection: fingertip-prick blood sample collection.

##### ②Calculation of GI

The GI was calculated with the reference glucose whose IAUC set as 100 (white bread is set as 71), the GI value of the product is:

$$I_{mean} = \text{Test food IAUC} / \text{glucose IAUC} \times 100$$

##### ③Satiety evaluation

The VAS scale was used for the comparison of satiety. Subjects' satiety change were record at 8 time points (0 min, 15 min, 30 min, 45 min, 60 min, 90 min and 120 min) within 2 hours after eating, and the data were collected and processed.

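### Satiety is compared by one-way ANOVA or paired t-test without the 0-minute VAS as a covariate, which gives up precision in the 12-versus-18 contrast

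*Protocol*

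**What the plan says.** Section 11 ③ of the Protocol says "The VAS scale was used for the comparison of satiety" and describes the measurement as "satiety change were record at 8 time points (0 min, 15 min, 30 min, 45 min, 60 min, 90 min and 120 min". So a rating at 0 min is part of the schedule, and the variable is called a change. The text does not say whether the analysis uses the change from 0 min, the raw rating at each time, or a summary over the two hours. (The sentence announces eight times and lists seven.)

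Section 11 covers the analysis of everything collected: "All data were processed and compared using origin 2021 and Graph Prism 7.0", and "Data were analyzed by one-way ANOVA and paired t-test". It names no covariate and no model with a baseline term.

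Section 8 has 12 subjects, randomly selected from 30, take the tests of the experiment groups, and 18 take the control test.

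Glucose is treated differently. Section 7 makes the outcome an incremental area under the curve, expressed relative to the same participant's reference food. Section 11 gives the time-point values a descriptive role: "the means and standard deviation (SD) were calculated for the normality test".

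**The concern.** People arrive at a session more or less hungry, and that starting level probably predicts how full they say they are afterwards. Where control and extract breads are eaten by different people, in groups of 12 and 18, part of the spread in post-meal ratings is simply spread in starting level. A rating that could remove that part is listed at 0 min, but the named tests use it either not at all (raw scores) or at a fixed weight of one (change scores). The fixed weight is too heavy when the correlation is modest, because the change score then takes on the full error of a single baseline rating.

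At stake is how precisely a satiety difference can be estimated in a small study. Unlike GI, which is normalised to the participant's own reference value, satiety has no stated normalisation.

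**Working it through.** **Inputs.** Group sizes are 12 and 18 (section 8), total 30, taken as separate people. The Protocol gives no VAS standard deviation and no correlation between the 0-min rating and the post-meal outcome. So results are in SD units, and the correlation ρ is assumed over 0.3 to 0.7, with 0 as the unfavourable case. Also assumed: equal SDs at baseline and after the meal, one common slope, and a 0-min rating made before the first bite. The Protocol has no precision figure for satiety to reproduce; its sample-size figure in section 6 concerns GI only.

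**Step 1: the raw contrast.** SE = SD × √(1/12 + 1/18) = 0.373 SD. The difference detectable with 80% power (two-sided 5%, normal approximation) is (1.960 + 0.842) × 0.373 = 1.04 SD. The same 0.373 is the SD of the chance gap in starting level between the groups, in baseline SDs.

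**Step 2: variance factors relative to raw.**
- Raw: 1.
- Change from 0 min: 2(1 − ρ).
- Baseline as covariate: (1 − ρ²) × 27/26 = 1.038(1 − ρ²). The factor 27/26 = 1 + 1/(30 − 4) is the small-sample price of estimating the slope.

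**Step 3: SE ratios.** Raw/adjusted = √[1 / (1.038(1 − ρ²))]; change/adjusted = √[2(1 − ρ) / (1.038(1 − ρ²))].

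| ρ (assumed) | Adjusted variance | Change variance | SE raw / adjusted | SE change / adjusted |
|---|---|---|---|---|
| 0 | 1.038 | 2.0 | 0.98 | 1.39 |
| 0.3 | 0.945 | 1.4 | 1.03 | 1.22 |
| 0.5 | 0.779 | 1.0 | 1.13 | 1.13 |
| 0.7 | 0.530 | 0.6 | 1.37 | 1.06 |

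Against raw scores, adjustment breaks even near ρ = 0.2, where its factor is 0.997. At ρ = 0 it costs √1.038 = 1.02, about 2% in SE. Change scores are worse than raw below ρ = 0.5.

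**Step 4: what this means for detection.** Take a true difference of 1.04 SD, for which the raw comparison has 80% power. Adjustment gives 82%, 89% and 97% at ρ = 0.3, 0.5 and 0.7; change scores give 66%, 80% and 95%. The detectable difference with adjustment is 1.02, 0.92 and 0.76 SD.

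**Step 5: bias or precision?** In 40,000 simulated random selections at each of ρ = 0.3, 0.5 and 0.7, the raw two-sample t-test had a mean error of essentially zero and a false-positive rate of 4.9% to 5.0%. A starting gap above 0.5 SD arises in 18% of selections. Within those, the rate was 7%, 11% and 17%. The overall error rate is therefore held, and what adjustment removes is avoidable variance.

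**The case against.** The strongest reply is that a baseline covariate is commonly left to the statistical analysis plan, which is not at hand. That stands for the detail of a model and helps keep the point small. It does not dispose of it, because section 11 does fix the tests for all data, and as named they carry no covariate.

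Three stronger readings are tempting and are not supported:

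- **That the 0-min VAS is ignored.** A reader might infer this from the named tests. But section 11 ③ says "Subjects' satiety change were record at 8 time points", and both tests can be run on change scores. The supportable statement is that the variable is undefined and that either version uses the baseline inefficiently.
- **That a starting difference biases the result towards or against the extract.** Section 8 states random selection, and Step 5 shows that the overall error rate holds. Only conditional on a large gap does the false-positive rate rise.
- **That glucose is compared raw at each time point.** No such test is stated. Time-point values serve means, SDs and a normality check, and the outcome is an incremental area. A time-point test could only be inferred from the sentence that all data were compared.

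It is also fair to say that the ratios describe only the independent 12-versus-18 contrast. Comparisons among extract levels, which serve the dose-effect aim in section 4, are made within the same 12 people if each takes every level; the design figure is not shown. There the between-group gap is absent, though session-to-session differences in starting level remain. Finally, the study is exploratory, and section 4 names glycemic index and sensory quality, not satiety, as its purpose. Both points limit the importance.

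**Conclusion.** The point holds as a minor one about efficiency. As described, the satiety comparison does not make efficient use of the 0-min rating. In the 12-versus-18 contrast this costs about 3% to 37% in SE if raw scores are used, and 22% down to 6% if change scores are used, as the assumed correlation goes from 0.3 to 0.7. These figures rest on that correlation, on equal SDs, on separate groups of 12 and 18, and on a 0-min rating made before eating. Below a correlation of about 0.2 there is nothing to gain over raw scores, and the loss is at most about 2%. No bias is shown, no size is claimed for comparisons within the 12, and no fault is claimed in the glucose outcome.

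**What to change.** In sections 11 and 11 ③:

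- Define one satiety outcome in advance, for example the mean post-meal VAS over the 120 minutes.
- Analyse it with that session's 0-min VAS as covariate, and state that this rating is made before the first bite.
- Add a participant term where the same people take several breads.
- If a time-point glucose comparison is made at all, use the mean of the −5 and 0 min values as its covariate. Otherwise no change is needed for glucose.
- Correct the count or the list of rating times while editing the sentence.

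The cost is one degree of freedom and slightly more analysis work, mainly because the participant term calls for a repeated-measures model in place of a plain ANOVA. No extra data, visits or participants are required.
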